### Trial design

The design of the planned bi-centric randomized controlled superiority trial will be based on a within-between interaction group design with three groups (WLC, APP, TG-APP) and parallel group assignment. The primary outcome criterion is the change in symptom severity of SAD, as measured by the Liebowitz Social Anxiety Scale (LSAS) [21, 22]. It will be assessed by trained, blinded, independent raters at pre-treatment, post-treatment, and 6 months after post-treatment (follow-up). The planned allocation ratio for TG-APP vs. APP only vs. WLC will be 1:1:0.7.

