### Procedure

The study will be conducted in Germany at the outpatient psychotherapy unit of the Clinical Psychology department of the Goethe University of Frankfurt as well as the outpatient psychotherapy unit of the Clinical Psychology department of the Technische Universitaet Dresden and two further CBT training centers in Dresden. For reporting purposes, we followed the SPIRIT reporting guidelines [27].

In the first step, all persons that register for participating in the study will be screened using an online self-report assessment. If participants exceed the cut-off of 25-points or find themselves within the criteria for social anxiety disorder, they are referred to another online self-assessment and then invited for an interview with a clinical rater. Beforehand, they will be informed about the study and provided with written informed consent (either personally or via email if necessary). Interviews to determine the patient's formal diagnosis are conducted by blinded and independent psychologists (with at least a master’s degree) who have been trained in the appropriate interviews. Eligible patients are then randomly assigned to one of three groups (WLC, APP, TG-APP). Participation in each of the groups lasts 3 months. Participants in the WLC group then have the option of using the app if they wish. The outcome measures will be assessed by blinded and independent raters at baseline, post-treatment (3 months after start), as well as 6 months after the post-treatment interview (follow-up). Furthermore, participants will complete self-report questionnaires online at baseline, at mid-treatment (at 6 weeks), post-treatment (at 12 weeks), and follow-up (at 36 weeks; see Fig. 1 for the study flowchart). Interviewers will remind patients to fill out the self-report questionnaires and if necessary, patients will be contacted by the study coordinator to complete the missing questionnaires.

Prior to the start of the study, we will conduct a pilot study to improve usability and evaluate the mobile application and the applicability of therapist-guided video therapy and the videoconferencing tool.

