### Allocation and randomization

Randomization is performed using a randomization list in which, based on 165 randomly generated numbers sorted by size, each of the available options is assigned according to the planned sample size (WLC = 43, APP = 61, TG-APP = 61). The list is then sorted by sequential number. A study coordinator who is not involved in the diagnosis or treatment process will enter the subjects into the randomization list according to the order of inclusion. The result is communicated to the patients via email and remains hidden from the clinical evaluators. The email to the participant contains the result and, if the person belongs to one of the two intervention groups, all the necessary information to use the app.

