### Outcomes

#### Primary outcome measure

We defined the clinician-rated Liebowitz Social Anxiety Scale (LSAS) [21, 22], as the primary outcome measure, a measure widely considered the gold standard in controlled studies on SAD. The LSAS is designed as an interview to assess fear and avoidance in 24 different social situations (rated on a 4-point scale from “not at all” or “never” to “severe” or “most of the time”). The LSAS demonstrated good internal consistency (Cronbach’s *α* = 0.96), validity and treatment sensitivity [30].

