Treatment satisfaction will be measured by using the Client Satisfaction Questionnaire (CSQ) [50], which we adapted slightly to match the use of the app. This 8-item questionnaire uses questions like “How satisfied are you with the amount of help you received?“. It showed satisfying internal consistency and concurrent validity [51, 52]. Social anxiety and social approach behavior will be measured using a modified version of the Social Phobia Weekly Summary Scale (SPWSS) [53], which will be assessed by participants weekly (for the APP and the TG-APP condition) and at pre, mid, post and follow-up assessments (for all conditions). The SPWSS covers ratings of anxiety, avoidance, self-focused attention, anticipatory worry, post-event rumination, and social approach behavior. We added questions asking for feelings of pleasure and pursuit of personal goals and changed the scale to a 0–100 scale. The SPWSS is sensitive to treatment effects and has good internal consistency [53].

Finally, we will also assess negative side effects which are specific to patients with SAD. Drawing on the results of Boettcher et al. [19], we developed a brief (7-item) scale with items covering the negative side effects that were considered most relevant by a group of experts (see Additional file 1). The items are rated on a scale from 0 (“do not agree at all”) to 5 (“fully agree”). Please note that the descriptive list of possible side effects is preliminary and may be slightly revised after the pilot study. As the list contains an open item, responses to this item will be evaluated after the pilot study and inclusion of further side effects in the list is possible should they be mentioned frequently.

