#### Data monitoring committee

There is no data monitoring committee and no independent auditing process. The quality of the data is assured by the blinded clinical raters and there are no known serious adverse effects. If serious adverse effects occur, they will be reported to the principal investigator, who will then interview the patient in question and refer them to a psychiatry if needed. Adherence to therapeutic measures is ensured by regular supervision by the principal investigators. Completeness of data will be regularly verified by the study coordinators.

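### Interviewers who very probably rate the LSAS blind also remind patients about self-report forms, which gives patients an avoidable occasion to disclose their arm near the post-treatment rating

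*Protocol article*

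**What the plan says.** **Primary outcome.** The Trial design section says of symptom severity on the LSAS: "It will be assessed by trained, blinded, independent raters at pre-treatment, post-treatment, and 6 months after post-treatment (follow-up"). The Primary outcome measure section adds: "The LSAS is designed as an interview to assess fear and avoidance in 24 different social situations".

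**Concealment.** Under Allocation and randomization: "The result is communicated to the patients via email and remains hidden from the clinical evaluators". Patients therefore know their arm, and raters are meant not to.

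**Reminders.** Under Procedure: "Interviewers will remind patients to fill out the self-report questionnaires and if necessary, patients will be contacted by the study coordinator". The sentence goes on to say that the coordinator's contact is for questionnaires that are missing. It directly follows the description of the online batteries at baseline and weeks 6, 12 and 36, which is written for participants in general.

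**Self-report that depends on the arm.** Under Self-rating scales, the modified Social Phobia Weekly Summary Scale (SPWSS) is a measure "which will be assessed by participants weekly (for the APP and the TG-APP condition"), and all conditions also complete it at the pre, mid, post and follow-up assessments. The same section describes the Client Satisfaction Questionnaire (CSQ) as one "which we adapted slightly to match the use of the app".

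**Completeness.** Under Data monitoring committee: "Completeness of data will be regularly verified by the study coordinators".

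**The concern.** Patients cannot be blinded here, so rater blinding is the main protection against assessor bias in an interviewer-scored primary outcome. The Procedure section asks people who must stay blind to raise questionnaires with patients who know their allocation and whose questionnaire load depends on it. A patient might answer by asking whether the weekly form is meant, or by saying that they have no app.

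The contrast most exposed is active treatment against wait-list, because the weekly SPWSS schedule separates the two app arms from WLC but not from each other. That contrast is Hypothesis 1a and the wait-list part of Hypothesis 1b. It is also the comparison in the possible interim analysis linked to licensing, which names the LSAS among its outcomes. The protocol leans further on rater blinding in the Data monitoring committee section, which cites the blinded raters as the assurance of data quality and states that there is neither a monitoring committee nor an independent audit.

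**Working it through.** No stated figure depends on this point, so there is nothing to reproduce. The check sets the sections side by side.

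1. **Are the interviewers the LSAS raters?** The text does not say so in one sentence, but the inference is strong. The LSAS is obtained by interview (Primary outcome measure). Blinded, independent raters assess it (Trial design, Procedure). The Organizational structure section lists a single role, clinical raters, that covers both eligibility and outcome evaluations, and it lists no separate interviewer.

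2. **What do the interviewers do?** They remind. Pursuing missing forms belongs to the study coordinator in the same sentence, and checking completeness belongs to the coordinators under Data monitoring committee.

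3. **Which forms does the reminder cover?** Its position suggests the batteries at weeks 0, 6, 12 and 36. Its wording does not confine it to them: "Interviewers will remind patients to fill out the self-report questionnaires".

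4. **Which self-report differs by arm?** The weekly SPWSS schedule does so explicitly, being confined to APP and TG-APP. The SPWSS as an instrument does not, since all arms complete it at the main assessments. The CSQ is worded for app use, but the text does not state its arms, and the schedule figure (Fig. 2) is not available here, so no conclusion can be drawn about who receives it.

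5. **When could a reminder matter?**

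| Wave | Rater assessment listed? | Consequence of a reminder by the rater |
|---|---|---|
| Baseline | Yes | Harmless: it precedes randomisation |
| Week 6 | No | Read literally, a contact during treatment that no rating requires; disclosure would come before the primary rating |
| Week 12 (post-treatment) | Yes | Close to the primary LSAS rating; the text does not say whether the reminder comes before or after scoring |
| Week 36 (follow-up) | Yes | Outside the primary baseline-to-post contrast; WLC patients may by then be using the app |

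The exposure that matters for the primary contrast is therefore at week 12, and at week 6 if interviewers also remind then.

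6. **Size.** Any bias in the contrast would be roughly the additional share of ratings unblinded by reminders, multiplied by the mean shift in score when a rater is unblinded. The document gives neither quantity, so the product cannot be computed from it.

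**The case against.** The case on the other side is substantial, and most of it stands.

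- **A reader might infer that raters chase patients for missing forms.** The document does not support this. The coordinator contacts patients about missing questionnaires, and the coordinators verify completeness.
- **A reader might infer that some questionnaires exist only in the app arms.** This too is unsupported. The SPWSS is used in all conditions and only its weekly frequency differs. The arms for the CSQ are not stated in the text.
- **A reader might infer that raters see which forms are outstanding.** Nothing says so. The questionnaires are online and identified by code.
- **A reader might infer that the reminder contradicts concealment.** It does not. A generic reminder about batteries common to all arms discloses nothing, and the sentence may well mean only that.
- **The added risk may be small.** The rater already conducts a long interview with a patient who knows the arm, so some chance of disclosure is inherent in the method. To bias the primary outcome, a reminder would have to come before scoring and prompt a spontaneous remark.
- **It is tempting to attach a number.** Assuming that 10% to 30% of ratings are newly unblinded, with a shift of 0.2 to 0.4 SD, gives 0.10 × 0.2 = 0.02 SD to 0.30 × 0.4 = 0.12 SD. Both inputs are pure assumption. Expressing the result as a share of a planned effect also depends on the denominator. Against the dropout-reduced APP effect of 0.35 it is 6% to 34%. Against the unreduced 0.5, which suits better because only patients actually rated can be affected, it is 4% to 24%. None of this is evidence about this trial.
- **Two of the three outcomes named for the possible interim analysis, the WHO-QOL-BREF and the PDI, are self-reports.** Rater unblinding cannot shift them.

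What survives is narrow. The reminder is a stated procedure, it is given to people who are very probably the blinded raters, and nothing restricts it to the common batteries or places it after LSAS scoring.

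**Conclusion.** The Procedure section creates an avoidable occasion for patients to disclose their allocation to the rater around the post-treatment LSAS interview. This is a possible risk that follows from who is given the reminder task and how loosely it is worded. It is not evidence that unblinding will occur, and it is not a contradiction with the Allocation and randomization section.

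The conclusion rests on two points: that the interviewers are the LSAS raters, which is a strong inference but not stated outright, and that reminders are given after randomisation, which the sentence allows but does not spell out. The size of any bias cannot be derived from the document. The change is worth making because it costs almost nothing and protects the primary outcome; it is a cheap improvement and not the repair of a demonstrated error.

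**What to change.** Amend the Procedure section so that, after randomisation, all questionnaire reminders come from the study coordinator, and state that raters have no access to questionnaire completion status. The coordinator is the natural choice: this role already holds the randomisation list and stands outside diagnosis and treatment, checks completeness, and contacts non-completers.

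If raters must keep some part in reminders, the minimum is one clause that limits them to a generic reminder about the batteries common to all arms, given after the LSAS has been scored. Reminders at the baseline interview can stay as they are.

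The cost is slightly more coordinator time. No new staff, instrument or visit is needed, and the sample size and analysis are unaffected.

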### Ethical issues

The study was approved by the Ethics Committee of the Department of Psychology at Goethe University Frankfurt. If post-trial care is required (e.g., in case of serious adverse effects), this will be provided by the outpatient clinics in Frankfurt and Dresden, and participants will be referred to a hospital or psychiatric clinic if necessary.

### Recruitment

Advertisements for participation include print media (e.g., brochures or text in print media), posts on social media, and outreach to mental health professionals, inpatient and outpatient facilities, and general practitioners to identify appropriate participants.

### Eligibility criteria

Inclusion criteria:Current diagnosis of Social Anxiety DisorderWritten informed consent before the start of the studyAge: 18 to 65 yearsPossession of smartphoneFamiliarity with using apps

Exclusion criteria:Acute suicidalityActive substance abuse or dependenceSevere medical conditions (e.g., chronic cardiovascular disease)Severe depressionPsychotic disorderBipolar disorderBorderline personality disorderCurrent psychotherapeutic treatmentCurrent psychopharmacological treatmentNo proficient skills in the German language

Furthermore, patients may be withdrawn from the study for the following reasons:Request of patientPost-hoc observation of criteria for exclusionThreat to patient’s mental or physical health due to participating in the study

### Allocation and randomization

Randomization is performed using a randomization list in which, based on 165 randomly generated numbers sorted by size, each of the available options is assigned according to the planned sample size (WLC = 43, APP = 61, TG-APP = 61). The list is then sorted by sequential number. A study coordinator who is not involved in the diagnosis or treatment process will enter the subjects into the randomization list according to the order of inclusion. The result is communicated to the patients via email and remains hidden from the clinical evaluators. The email to the participant contains the result and, if the person belongs to one of the two intervention groups, all the necessary information to use the app.

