#### Primary analysis

For our primary analysis, we plan to fit a linear mixed model with random intercepts for participants in the R package lme4 [61]. We take the *z*-standardized values of the Liebowitz Social Anxiety Scale (LSAS) as the outcome variable, and time and treatment condition as categorical predictors, for which we specify an interaction term. The estimated effects of the predictor variables indicate the change in LSAS from baseline at week 0, which we choose as the reference category, to post-treatment.

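### Two-city trial with a single unstratified allocation list and no centre term in the models: chance centre imbalance is neither prevented nor adjusted for, at a small cost in precision that is cheap to avoid

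*Protocol article*

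**What the plan says.** The Trial design section calls this a "planned bi-centric randomized controlled superiority trial". The Procedure section names the Frankfurt and Dresden university outpatient units "and two further CBT training centers in Dresden".

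The Allocation and randomization section describes one list for the whole trial: "Randomization is performed using a randomization list in which, based on 165 randomly generated numbers sorted by size", with arm totals fixed in advance ("WLC = 43, APP = 61, TG-APP = 61"). A study coordinator outside diagnosis and treatment "will enter the subjects into the randomization list according to the order of inclusion". Neither centre strata nor blocks are mentioned.

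The Primary analysis section specifies a linear mixed model for standardised LSAS with a participant random intercept and "time and treatment condition as categorical predictors", plus their interaction. The Secondary analyses section carries the same predictors over to the other outcomes and adds app usage time and number of behavioural experiments. It tests hypotheses 1b and 2b through pairwise differences between conditions at a given time, such as post-treatment. Centre appears in none of these models.

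**The concern.** A single list used in order of inclusion fixes the overall totals but not the split of arms within each city. One arm can by chance draw noticeably more of its patients from one city than another does. If the cities differ in case mix or in how much patients improve, that difference passes into the arm contrasts. With no centre term, the model cannot take it out again.

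The contrast with least room is TG-APP versus APP, where the planned difference after the dropout reduction is 0.64 − 0.35 = 0.29 SD. At stake is precision in the one trial that is run, not the validity of the randomisation.

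**Working it through.** **Inputs from the protocol article.** Arm sizes 43/61/61 (Allocation and randomization). Effects against WLC of 0.35 and 0.64, intercept and residual variances of 0.5 each, α = 0.05, and a stated power of 84% (95% CI 80.0 to 87.0, 500 simulations) at 41/61/61 (Design and sample size).

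**Assumptions, because the article gives no figures.** Half the patients come from each city (82 v 83), with other splits as a sensitivity check. The centres differ by 0.2 to 0.4 SD.

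**1. The plan's own power.** With two time points, the variance of change is 2 × 0.5 = 1. The 2-df noncentrality is λ = Σ n(δ − mean δ)². At 41/61/61 the mean is (61 × 0.35 + 61 × 0.64)/163 = 0.370, λ = 10.08, and power is 81.9% (81.5% by a 20,000-run simulation). This lies inside the stated interval, so the figure is reproduced within simulation error. At the final 43/61/61, λ = 10.36 and power is 82.9%.

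**2. How uneven the centre shares can be.** The SD of the difference in centre share between two arms is √[p(1 − p) × (165/164) × (1/n₁ + 1/n₂)]. At p = 0.5:

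- APP v WLC: 0.5 × 1.003 × √(1/61 + 1/43) = 0.100, or 10.0 points.
- TG-APP v APP: 0.5 × 1.003 × √(2/61) = 0.091, or 9.1 points.

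Probabilities from multivariate hypergeometric draws at 50:50:

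| Difference in centre share | Some pair of arms | TG-APP v APP only |
|---|---|---|
| more than 10 points | 51% | 24% |
| more than 15 points | 25% | 8.6% |
| more than 20 points | 10% | 2.4% |

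At 70:30 the TG-APP v APP column becomes 20%, 6% and 1.4%. For some pair of arms, a difference of at least 10 points has probability 53% at 60:40, 49% at 70:30 and 38% at 80:20.

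**3. Which centre differences matter.** The primary estimate is a difference in change, so a centre difference that is the same at both times drops out. In a simulated trial the two interaction estimates were −0.2962 and −0.6297 both without and with a centre main effect. The post-treatment pairwise contrast is cross-sectional, so the same level difference stays in it. With 34/61 v 25/61 patients from one city (9/61 = 14.8 points), adding a 0.4 SD level difference left the change contrast at −0.308 and moved the post-treatment contrast from −0.062 to −0.003, a shift of 0.059 (0.148 × 0.4). A centre difference in change affects both kinds of contrast.

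**4. Size of the shift.** Shift = imbalance × centre difference: 0.15 × 0.2 = 0.03 SD and 0.15 × 0.4 = 0.06 SD. The standard error of TG-APP v APP is √(2/61) = 0.181, both for change (variance 1) and at post-treatment (0.5 + 0.5 = 1). The shift is therefore 0.03/0.181 = 0.17 to 0.06/0.181 = 0.33 standard errors.

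**5. Power lost by leaving out centre × time.** An unmodelled centre difference γ in change raises the variance of change to 1 + γ²/4 at 50:50:

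| γ | Variance of change | Power | Loss from 82.9% |
|---|---|---|---|
| 0.2 | 1.010 | 82.6% | 0.4 points |
| 0.3 | 1.0225 | 82.1% | 0.9 points |
| 0.4 | 1.040 | 81.4% | 1.6 points |

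Losses are taken from unrounded values.

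**6. Bias, error rate and the price of adjusting.** Over 8,000 simulated trials per scenario, the unadjusted estimates averaged the true effects to within simulation error. Type I error without a centre term was 5.1% to 5.4%. With no centre effect at all, adjusting left power at 82.8% against 83.0% unadjusted.

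**The case against.** Unstratified randomisation with fixed totals is valid, and a completed list delivers exactly 43/61/61, including the 43 WLC patients that the licensing calculation asks for. Averaged over lists there is no bias. The app is the same for everyone, and the video sessions follow one manual under supervision, so a large centre difference in change is not obvious. All of this stands, and it keeps the point small.

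A reader might infer more than the documents support, in three ways.

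- **That LSAS ratings are tied to sites, so rater habits contaminate the arms.** The article calls the raters trained, blinded and independent; it does not assign them to sites.
- **That any centre difference enters the primary result.** Stable level differences cancel from group × time with complete data, so a centre main effect alone would not change that estimate.
- **That one list in four threatens the 0.29 SD contrast.** The 25% figure is for any of the three pairs. For TG-APP v APP a gap above 15 points occurs in 8.6% of lists, about 1 in 12.

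Therapist differences do not rescue the stronger reading either. Only TG-APP has therapists, so this is a within-arm matter that centre terms do not isolate.

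It can also be said that a condensed article leaves covariates to the analysis plan. That carries less weight here, because the article itself sets out the list mechanism and names the model predictors.

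**Conclusion.** The point holds as an inexpensive improvement, not as an error that invalidates the result. Neither the allocation nor the models, as described, deal with chance centre imbalance in a trial run in two cities, and a 10-point gap between some pair of arms is about as likely as not. The effect on conclusions is modest: a fraction of a standard error in a contrast and at most a point or two of power over the assumed range. Level differences matter only for the post-treatment pairwise contrasts used for hypotheses 1b and 2b; differences in change matter for the primary test as well.

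The sizes rest on the assumed centre split and centre difference, neither of which the article gives, and on complete data. The absence of centre strata and centre terms from the text does not depend on these assumptions.

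**What to change.** 1. Add centre (Frankfurt v Dresden, with the two training centres counted under Dresden) and centre × time as fixed effects to the primary and secondary models. The main effect protects the post-treatment contrasts; the interaction with time protects the change contrasts. This can be done whether or not allocation has started, provided it is fixed before outcomes are analysed.
2. If no patient has yet been allocated, replace the single list by one concealed list per city in permuted blocks of varying size at about the planned ratio ("TG-APP vs. APP only vs. WLC will be 1:1:0.7"). For example, an equal random mix of blocks of 8 (3:3:2) and 11 (4:4:3) gives 7:7:5, or 1:1:0.71. If allocation has begun, keep the existing list and make only the first change.

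Cost: regenerating the list and carrying two extra model terms, with essentially no loss of power if the centres do not differ. Final totals may miss 43/61/61 by a few patients, so the WLC count should be watched against the 43 required for the licensing analysis.
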